**Aims and hypotheses**
Aim 1: the first aim is to evaluate the implementation effectiveness of digital peer support training between emerging adults providing support (befrienders) and emerging adults seeking help (seekers).Research question 1a: is Acceset digital peer support training an effective training curriculum in providing peer support?Hypothesis 1a: the digital peer support training is effective for befrienders in providing peer support, as demonstrated by the adoption of and fidelity to the training curriculum.Research question 1b: is the Acceset text-based intervention (ie, the platform) feasible and acceptable (ie, safe and timely) as an ongoing mechanism of support for seekers and befrienders?Hypothesis 1b: digital peer support is feasible and acceptable in offering support for emerging adults’ mental well-being, which is evidenced by 2 indicators:The engagement of the seeker-befriender-moderator interaction across the 4 time points—baseline (before the intervention), 3 weeks (conclusion of the intervention), and 6 and 9 weeks (carryover effect assessment)—that is indexed by the waiting period for seekers to receive a response. Delays are defined as a >48-hour waiting period and will be categorized based on the following reasons: (1) technical factors (eg, the befriender is not able to log into the platform to respond in time) and (2) human factors (eg, the befriender drops out from the study, and no replacement is found in time). An acceptable response time is within 48 hours, and this is emphasized during Acceset digital peer support training for befrienders [37].The use of technical features of the Acceset platform that is measured by the seeker dropout rate at each stage of engagement with the Acceset platform, the number of visits on the study registration website, the number of participants who registered with Acceset, the average number of letters exchanged, and the average number of emotion and functional adjustment stickers and motivation graphic interface formats used [37].Research question 1c: is the Acceset text-based intervention (ie, the platform) feasible and acceptable (ie, safe and timely) as an ongoing mechanism of support that identifies individuals who are at an unacceptably high risk of mental health conditions?Hypothesis 1c: digital peer support is feasible and acceptable in offering support for emerging adults’ mental well-being by identifying individuals who are at an unacceptably high risk of mental health conditions related to depression and suicidality, which is measured before and during engagement based on 3 means—specifically, the Acceset algorithm detection of the content of the letters, the moderators’ vetting of the content of seekers’ letters, and the seekers’ self-report responses to the 9-item Patient Health Questionnaire [38] (refer to the Implementation Outcomes section for details [37]).Aim 2: the second aim is to elucidate whether Acceset digital peer support harnesses the 4 components of emerging adult mental health—mattering, selfhood, compassion, and mindfulness.Research question 2a: does Acceset digital peer support enhance the 4 components among seekers and befrienders?Hypothesis 2a: Acceset digital peer support (training) increases the 4 components among befrienders (before and after training) and seekers (over the course of the study across 4 time points).Research question 2b: is Acceset digital peer support effective in improving emerging adult mental well-being?Hypothesis 2b: digital peer support leads to significantly better mental well-being of seekers compared with the control group. This effect is sustained beyond the period of the intervention.Aim 3: the third aim is to investigate the mechanism of change in emerging adult mental well-being involving digital peer support (delivered by the Acceset platform).Research question 3: what is the mechanism explaining the change in emerging adult mental well-being involving digital peer support?Hypothesis 3: the initial level and rate of change (ie, growth factors) of befrienders’ web-based support positively predict the growth factors of seekers’ psychological well-being in accordance with latent growth curve modeling.

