### Participants and Study Setting

We plan to recruit 130 participants (100 seekers and 30 befrienders) at the National University of Singapore (NUS) to engage with the Acceset intervention in accordance with an Institutional Review Board–approved protocol. Participants will be recruited via the Research Participation program within the Department of Psychology at NUS, where students will be awarded credits as part of the introductory courses for psychology. During recruitment, inclusion and exclusion criteria screening will be conducted via self-reporting. Participants qualified for inclusion (seekers) will be randomized into 2 arms. The seekers (n=50), befrienders (n=30), and moderators (n=30) in arm 1 will use Acceset for 3 weeks. The control group (n=50) in arm 2 will be wait-listed for Acceset use. It should be noted that the wait-listing approach is a standardized approach for RCTs pertaining to digital mental health [37,39,40].

We will recruit age- and gender-matched individuals from NUS. The 4–time-point questionnaire battery of arm 1 will be used to compare the mental well-being and help-seeking behavior with those in arm 2 [37]. Moderators will be recruited from the Singapore Executive Counselling and Training Academy. If an unacceptably high risk of depression and suicidality is detected at any time point by the moderator, who is a certified counselor, they will reach out to the participant, who will be directed to different clinical mental health support providers, including counseling centers and hotlines, on the NUS campus. On the basis of power analysis and the finding that 20% to 40% of the emerging adults enrolled in an IHL typically experience distress, this sample will provide a sufficiently powered comparator group.

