The moderation protocol at the participant recruitment stage entails the screening of seekers using a validated psychological scale—the 9-item Patient Health Questionnaire (PHQ-9)—to exclude individuals at high risk of depression and suicidality. During the intervention phase, befrienders are also trained to alert moderators when seekers are at an unacceptably high risk of depression and suicidality, and the moderator vets all the letter exchanges between the seekers and befrienders for content of high negativity and suicidal thoughts and expressions. This moderation protocol aims to identify seekers who are at an unacceptably high risk of depression and suicidality and refer them to an appropriate mental health care provider, including counseling centers and hotlines, on the NUS campus.

Each befriender will provide support to 3 seekers, receive notification from the Acceset platform on incoming letters, and work in partnership with the moderators to address the seekers’ issues during the 3 weeks of letter exchange. Befrienders have the choice to discontinue the letter exchange with seekers if they feel discomfort having to address issues that they find challenging by informing trained moderators. Given the sensitive nature of the letter content, there may be issues that befrienders will be exposed to that they are not fully comfortable with and may cause distress. Therefore, it is a deliberate design to ensure that the befrienders are not left on their own in handling cases and that they work in partnership with the 2 trained and certified moderators to address the seekers’ issues. The first point of contact for the befriender will be the 2 trained and certified moderators. In such cases, the befriender’s workload decreases to 2 seekers.

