#### Mechanism of Action

For research question 3 and hypothesis 3, we will elucidate the mechanism of change that links digital peer support intervention to emerging adult mental well-being (Figure 3). Specifically, we will assess whether and how the level at the start of the study and the rates of change from baseline to weeks 3, 6, and 9 in befrienders’ support relate to seekers’ mental well-being.

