The following approaches will be used for data analysis and interpretation. Independent-sample 2-tailed *t* tests will compare the intervention and control groups. Bonferroni post hoc tests will control for multiple comparisons. For both the intervention and control groups, additional independent *t* tests will compare seekers who provided data across all 4 time points with those who dropped out from the study for different reasons to ascertain if the sample with data across all 4 time points and the sample with fewer data points bias our results. For instance, seekers may drop out when risk assessments identify them as having a high risk of depression and suicidality during the course of the study. There will also be instances when befrienders discontinue the letter writing because of the sensitive nature of the letter content that may cause distress and befrienders not being fully comfortable, and the system will inform the seekers and obtain their consent to end the letter thread instead of continuing the conversation with a new befriender. Second, each participant’s emotional experiences disclosed on Acceset will be extracted based on the definitions of the 4 components of psychological well-being. Latent Dirichlet allocation analyses in R (R Foundation for Statistical Computing) and content analysis will be used [37,60,61].

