Latent growth curve modeling (LCM) will investigate the mechanism of change involving the trajectories of peer support in predicting the change in psychological well-being [59]. LCM delineates whether and how the exposure to the intervention changes over time with psychological outcomes by estimating and comparing different baseline latent growth models, including linear, quadratic, and nonlinear curve fitting (ie, optimal fit). In other words, LCM elucidates whether the trend in befrienders’ peer support predicts the trend in seekers’ psychological well-being (Figure 3). Current research assessing peer support intervention for the mental health of young people does not consider the mechanism of change. By establishing a change model, this protocol provides a basis for building the therapeutic potential of digital peer support that harnesses the components of emerging adult mental well-being to reduce psychological symptoms. Specifically, LCM elucidates whether and how the intervention affects the development of psychological symptoms and how they unfold over time among emerging adults. This finding provides actionable knowledge for timely and relevant digital peer support.

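### The latent growth model is said to show whether the intervention affects symptoms, but as described it tests only a non-randomised befriender-to-seeker association within arm 1

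*Protocol article*

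**What the plan says.** The protocol article describes the growth model in the same terms throughout.

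- Textbox 1 (Aims and hypotheses), hypothesis 3: "the initial level and rate of change (ie, growth factors) of befrienders’ web-based support positively predict the growth factors of seekers’ psychological well-being".
- Mechanism of Action: the study will assess whether the starting level and the "rates of change from baseline to weeks 3, 6, and 9 in befrienders’ support relate to seekers’ mental well-being".
- Data Collection, Management, and Analyses: "LCM elucidates whether the trend in befrienders’ peer support predicts the trend in seekers’ psychological well-being".
- Discussion, Principal Findings, item 5: the same relation again.

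Data Collection, Management, and Analyses then adds a wider claim for this model: "LCM elucidates whether and how the intervention affects the development of psychological symptoms and how they unfold over time among emerging adults". The Introduction (Aims, Research Questions, and Hypotheses) names the same question, whether and how digital peer support acts on symptoms, as a gap that the study is meant to fill.

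On the arms, Participants and Study Setting says: "The seekers (n=50), befrienders (n=30), and moderators (n=30) in arm 1 will use Acceset for 3 weeks". It continues: "The control group (n=50) in arm 2 will be wait-listed for Acceset use".

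The comparison of arms is planned separately. Hypothesis 2b sets seekers against controls. Clinical Outcomes plans change from baseline at 3, 6 and 9 weeks in both groups. The analysis section says that independent-sample t "tests will compare the intervention and control groups".

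**The concern.** Whether the intervention affects symptom development is a question about two trajectories, with Acceset and without it. Its null hypothesis is that these are equal on average. The LCM path has another null: among seekers who have a befriender, the befriender's trend is unrelated to the seeker's trend. Wait-listed seekers have no befriender during the comparison, so they carry no information on that path.

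Either null can be true while the other is false. If the sentence on the LCM were taken at its word, a path near zero could be reported as no effect when seekers as a group improved, and a positive path could be reported as an effect when the arms did not differ. Nor is the path protected by randomisation. Under Peer Emotional Disclosure, befrienders select the seekers they prefer to support, and under Participants and Study Setting they may stop when the letters distress them. Falling support can thus follow from a seeker's worse state as well as precede it.

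**Working it through.** **Plan's own figure.** The article states no figure for the LCM. For the trial it gives 50 seekers per arm, a .05 significance level and 80% power, with no target effect or SD, so the sample size cannot be reproduced. Solved backwards by the normal approximation, 50 per arm detects d = (1.960 + 0.842) × √(2/50) = 2.802 × 0.2 = 0.56. This concerns a comparison of arms, not the growth path.

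**Algebra.** Let S be a seeker's slope, B the slope of that seeker's befriender, δ a gain shared by all arm 1 seekers, and β the dependence on the befriender.

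- Arm 1: S = α + δ + βB + e
- Arm 2: S = α + e
- LCM path, arm 1 only: cov(S, B)/var(B) = β + cov(e, B)/var(B)
- Arm contrast: δ + β·mean(B)

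Three results follow.

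1. δ does not appear in the path. If β = 0 and e is unrelated to B, the path is zero for any δ, and its test rejects at its nominal level.
2. If β > 0 but δ + β·mean(B) = 0, the path is positive and the arms do not differ.
3. If befriender choice or discontinuation links B to e, the path can be positive with β = 0 and δ = 0.

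**Illustration.** Inputs from the article: 50 seekers per arm, 30 befrienders, weeks 0, 3, 6 and 9, and "Each befriender will provide support to 3 seekers" (used as a maximum). Assumed, not from the article: intercept SD 1, slope SD 1 over 9 weeks, residual SD 0.5, and mean(B) = 0. Each case has 4,000 simulated trials. Slopes are least-squares estimates. The path is the regression of arm 1 seeker slopes on befriender slopes, a two-step stand-in for the LCM. The arm comparison is a t test on slopes.

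| Truth | Path rejects | Arm comparison rejects |
|---|---|---|
| δ = 0, β = 0 | 4.8% | 5.5% |
| δ = 0.7, β = 0 | 5.1% | 82.8% |
| δ = 1.0, β = 0 | 5.5% | 98.6% |
| δ = 2.0, β = 0 | 5.7% | 100% |
| δ = 0, β = 0.6 | 73.8% | 6.3% |
| δ = 0, β = 1.0 | 96.6% | 8.2% |

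Hand check of the second row: with time scaled to 0, 1/3, 2/3, 1, the sum of squared deviations is 0.556. The slope estimate has variance 1 + 0.25/0.556 = 1.45, so its SD is 1.204. Then d = 0.7/1.204 = 0.581, and 0.581/0.2 − 1.960 = 0.95, which is a power of about 83%.

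The first four path rates differ only by simulation noise, since a constant shift in S leaves the regression on B unchanged. The arm comparison slightly exceeds 5% in the last two rows because seekers who share a befriender are correlated.

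**The case against.** The strongest reply is that the article does not rely on the LCM to establish effectiveness. Hypothesis 2b, the two-group change comparison under Clinical Outcomes and the between-arm t tests do that. The Discussion lists the effect against control (item 4) apart from the mechanism (item 5). This stands. A reader might infer that the trial would miss a benefit shared by all seekers; the documents do not support that, because a randomised comparison is planned. Nor does the article say that a null path will be reported as no effect. That is a risk of the wording, not a stated decision rule.

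It can also be said that the sentence is rationale and that the model matches hypothesis 3. That is so, but the sentence still states a conclusion that the model cannot give.

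A third reply is that an arm term may exist out of sight. Figure 3 is not shown, the measure of befrienders' support is not named in the text, and the analysis section speaks of exposure to the intervention. But the very next sentence restates that phrase as befriender trend predicting seeker trend, and every textual description agrees with it. Perceived social support could be measured in both arms, but it is not befrienders' support as hypothesis 3 words it. A fuller plan may add an arm term; the printed inference would still not follow from the printed model.

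Last, the simulated rates depend on assumed variances, and the two columns test different hypotheses, so the gap between them is not a loss of power. This also stands.

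**Conclusion.** The point holds as a fault in the inference attached to the LCM. As described, the model estimates a non-randomised association between befriender and seeker trends within arm 1 and cannot show whether the intervention affects symptoms. It is not a fault in the trial as a whole, because the randomised question has its own hypothesis and its own tests.

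The firm quantitative result is that the path test rejects at about 5% under any uniform benefit unrelated to befriender trend. It needs no variance assumption. The other rates (73.8% and 96.6% for the path with no mean benefit, and all the power figures for the arm comparison) are illustrative. The conclusion rests on the text as printed, with Figure 3 and the questionnaire appendix unseen.

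**What to change.** In Data Collection, Management, and Analyses:

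1. Describe the befriender-to-seeker path as a secondary association among arm 1 seekers, and delete the claim that it shows whether the intervention affects symptoms.
2. Take any statement on whether there is an effect from the randomised comparison. Either the planned between-arm tests will serve, or a seeker growth model on all 100 seekers with randomised arm predicting the slope.
3. If that growth model is added, label it as added after data collection. The Results section says that collection finished in June 2022 and analysis began in July 2022.

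The cost is a change of wording, a weaker mechanism claim and at most one extra post hoc model. No new data are needed.

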## Results

This protocol received approval from the Institutional Ethics Review Board of NUS in October 2021. Recruitment will commence in January 2022. Data collection began in March 2022 and was completed in June 2022. Data analysis started in July 2022 and is currently in progress. We aim to report the preliminary study outcomes in December 2022. The effect size will be analyzed using the Cohen *d* index with a significance level of .05 (95% reliability) and 80% power statistic [37]. A total of 100 seekers, 35 befrienders, and 2 moderators were recruited in January 2022.

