**Methods:**

A total of 100 participants (aged 19-25 years) from the National University of Singapore will be recruited and randomized into 2 arms. In arm 1 (n=50), the seekers will use Acceset with befrienders (n=30) as well as moderators (n=30) for 3 weeks. Arm 2 comprises a wait-listed control group (n=50). A questionnaire battery will be used to monitor seekers and befrienders at 4 time points. These include baseline (before the intervention), 3 weeks (end of the intervention), and 6 and 9 weeks (carryover effect measurement). Implementation outcomes of the intervention will involve evaluation of the training curriculum with respect to adoption and fidelity as well as user acceptability of the Acceset platform and its feasibility for broader deployment. Clinical outcomes will include mattering, selfhood, compassion, mindfulness, perceived social support, and psychological well-being scores.

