#### Clinical Outcomes

To address research question 2a and hypothesis 2a, we will examine whether the Acceset training curriculum can enhance the 4 components of psychological well-being among befrienders and seekers. We will compare the change in mattering, selfhood, compassion, and mindfulness scores of befrienders between baseline and following Acceset training (ie, before vs after training) and those of seekers over the course of the study. As for research question 2b and hypothesis 2b, we hypothesized that engagement with Acceset digital peer support will lead to improved mental well-being of the seekers compared with the control group and that this effect may be sustained beyond the period of the intervention. To assess these effects, we will evaluate the change in mental well-being of the participants in both study groups (intervention and control) after 3, 6, and 9 weeks from baseline using self-report questionnaires. Seekers will provide responses pertaining to help-seeking behavior beyond the Acceset platform at weeks 6 and 9 using the perceived social support measure in the questionnaire battery. We will assess the correlations of the 3 digital features—comprising emotion and functional adjustment stickers and motivation GIFs, which reflect seekers’ mental well-being during engagement with the platform—with their well-being scores from the questionnaires.

The scale or set of scales used to assess the clinical outcomes, including the 4 components of psychological well-being underpinning the Acceset training curriculum, measures of seekers’ well-being, and perceived social support, are outlined in the following paragraph.

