### Data Collection, Management, and Analyses

Acceset will serve as the data collection platform. Participants (both seekers and befrienders) will initially enter their details on the sign-up page, which includes role preference (seeker, befriender, or either), email, date of birth, gender, nationality, ethnicity, monthly household income, and password. The user will be required to answer the PHQ-9 to determine their eligibility. An email will also be sent to the users’ registered email address for verification. Once eligible individuals are selected and assigned their respective roles, they will be given a unique nonidentifying ID to participate in the study. Participants’ self-reported questionnaire responses at each time point and the digital letter exchange content will be securely stored and tied to their specific IDs. The data collected will be stored on the cloud servers of the leading author’s affiliated institution. Once the research concludes, the information will be downloaded to a Microsoft Excel sheet, and all personal information will be deidentified for data analyses.

A power analysis assessed the adequate sample size needed for the RCT to have sufficient power to detect valid effects. The intervention (n=50) and control (n=50) arms were derived from multiple dependent variables assessing implementation testing (ie, feasibility and utility) and clinical outcomes. To address any potential challenges with missing data, the Little Missing Completely at Random Test will address potential missing data via full information maximum likelihood imputation [37,59]. Maximum likelihood estimation is a method that ascertains the parameter values of a model using the mean and variance and maximizes the chance that the values generated are closest to those observed.

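### The 80% power claimed for 50 per arm has no stated effect size or primary comparison and is not reconciled with the plan's own Bonferroni rule or the dropout it expects

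*Protocol article*

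**What the plan says.** The Results section (and the Abstract) links Cohen d to "index with a significance level of .05 (95% reliability) and 80% power statistic". No value of d appears anywhere in the article.

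Data Collection, Management, and Analyses reports that a power analysis was done and describes the sample size this way: "The intervention (n=50) and control (n=50) arms were derived from multiple dependent variables assessing implementation testing". Participants and Study Setting calls the sample adequately powered, opening the sentence with "On the basis of power analysis and the finding that 20% to 40% of the emerging adults enrolled in an IHL typically experience distress".

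The analysis is set out in two sentences of Data Collection, Management, and Analyses: "Independent-sample 2-tailed *t* tests will compare the intervention and control groups", and "Bonferroni post hoc tests will control for multiple comparisons". The number of comparisons in the family is not given.

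The Abstract lists six outcomes: "Clinical outcomes will include mattering, selfhood, compassion, mindfulness, perceived social support, and psychological well-being scores". The Clinical Outcomes section describes seven constructs, because anxiety and depression are measured separately. For hypothesis 2b it compares the arms at weeks 3, 6 and 9. No outcome or visit is designated primary.

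The analysis section also expects some seekers to drop out, for example after a risk assessment. The target stays at 50 per arm throughout, and the Results section reports that 100 seekers were recruited.

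**The concern.** A power statement is about a particular test: its significance level, the effect to be detected and the number analysed. This one gives a level and a power but not the effect or the test. The rest of the article then describes features that change the other two inputs. Bonferroni across outcomes and visits lowers the per-test level below .05, and dropout lowers the number analysed below 50.

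The prevalence figure does not fill the gap. The share of students who are distressed affects how many eligible seekers can be found. It does not enter the power of a t test between two means.

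The phrase about Bonferroni post hoc tests is also open to two readings. As a pairwise correction among arms, it has only one pair to correct when there are two arms, so it changes nothing. As a correction across outcomes and visits, it means .05 is not the level of each test.

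Hypothesis 2b claims superiority with a sustained effect. Without a primary comparison or a defined family, it is unclear which result would count as success. A null result could also be read as coming from a trial shown to be adequately powered, which the printed inputs do not establish.

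**Working it through.** **Inputs from the article.** Two-sided independent-sample t test; n = 50 per arm; level .05; power 80%. Visits for the between-arm comparison: weeks 3, 6 and 9.

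**Inputs not given, so assumed or varied.** Effect size d (solved for below); size of the Bonferroni family k (3 to 21); loss to follow-up (20%, so 50 × 0.8 = 40 analysed per arm).

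**Step 1: can the stated 80% be reproduced?** No, because d is not stated. What can be found is the d at which 50 per arm gives 80% power on one test at .05.

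- Normal approximation: d = (z(.975) + z(.80)) × √(2/n) = (1.960 + 0.842) × √(2/50) = 2.802 × 0.2 = 0.560.
- Noncentral t, 98 degrees of freedom, noncentrality d × √(n/2) = 5d: d = 0.566, or 0.57 to two decimals.

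**Step 2: what Bonferroni does.** Replace .05 by .05/k and keep n = 50 per arm. The third column is power at d = 0.566, the value that gives exactly 80% for a single test.

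| k | Per-test level | Power at d = 0.566 | d for 80% power |
|---|---|---|---|
| 1 | .0500 | 80% | 0.57 |
| 3 | .0167 | 65% | 0.66 |
| 6 | .0083 | 56% | 0.71 |
| 9 | .0056 | 50% | 0.74 |
| 18 | .0028 | 41% | 0.79 |
| 21 | .0024 | 39% | 0.80 |

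Possible sources of each k:

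- 3: one well-being outcome at three visits.
- 6: anxiety and depression at three visits.
- 9: those two plus perceived social support at three visits.
- 18: the Abstract's six outcomes at three visits.
- 21: the seven constructs at three visits.

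**Step 3: what dropout does.** With 40 analysed per arm, a single test at .05 needs d = 0.63 for 80% power, and power at d = 0.566 is 71%. The 20% is an assumption; the article gives no rate.

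**The case against.** Three stronger readings are tempting, and the article does not support them.

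*A reader might infer that the 80% is wrong, or true only for one test at d = 0.57.* The article states no d, so 0.57 is a back-calculation. Fifty per arm gives at least 80% power for any d of 0.57 or more on one test. It also does so under Bonferroni if the assumed d was about 0.66 (3 tests) to 0.80 (21 tests) with no loss. The article says the size was derived from several dependent variables, so an adjusted calculation at a larger d cannot be excluded.

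*A reader might infer that power is about half of what is stated.* That fits only the families of 18 or 21 tests. The Clinical Outcomes section compares arms explicitly only for mental well-being under hypothesis 2b. The four components in hypothesis 2a are followed within befrienders and seekers. The between-arm family could be as small as 3 to 9 tests.

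*A reader might infer a false-positive risk of 60% to 66%.* Those figures are 1 − 0.95^18 = 0.60 and 1 − 0.95^21 = 0.66. They assume no correction and independent tests. The article says Bonferroni will be applied, and repeated scales in the same people are not independent.

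It is also fair to say that an article may leave the effect size, the family and the attrition allowance to a fuller document, and that the prevalence is cited alongside a power analysis rather than instead of one. So the missing details alone would not be a finding. What stands is that the printed text makes a positive claim of adequacy, partly on a figure irrelevant to it, beside a multiplicity rule and expected dropout to which the claim is not related. The planned full information maximum likelihood uses partial records but does not restore the full information of 50 per arm.

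**Conclusion.** The concern holds in a limited form. The claim of .05, 80% power and an adequate sample is unsupported as printed, because it lacks an effect size and a primary comparison and is not reconciled with the plan's own Bonferroni rule or expected dropout. It is not shown to be false.

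The size depends on an unstated family. Detectable d at 80% power runs from 0.57 (one unadjusted test) to between 0.66 and 0.80 (Bonferroni over 3 to 21 tests), all with 50 analysed per arm. At the single-test effect, power falls from 80% to between 65% and 39% over the same range. These figures assume two-sided t tests with equal variances. The family sizes and the 20% loss are assumptions.

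**What to change.** 1. Name one between-arm well-being outcome and one visit as primary for hypothesis 2b, tested at two-sided .05. Do this before between-arm results are viewed. The Results section says data collection ended in June 2022 and analysis began in July 2022, so if those results have already been seen, label the choice post hoc.
2. Replace the undefined Bonferroni post hoc tests with Holm over a listed set of the remaining between-arm outcome-by-visit tests. On the same family, Holm is never less powerful than Bonferroni.
3. Restate the power sentence, for example: *50 per arm gives 80% power for d = 0.57 on a single two-sided .05 test without loss, and for d = 0.63 if 40 per arm are analysed; other comparisons are not powered at this level.* If the power analysis used a different d or an adjusted level, report those values instead.
4. Remove the 20% to 40% prevalence as a basis for power. It can stay as background on recruitment.

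The cost is wording only, with no added participants. The stated power becomes less favourable, and the secondary outcomes carry less weight.
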